##### Integrated care protocol

A clinical occupational physician will be trained as RTW coordinator to fulfil an intermediate role between the patients' gynaecologist, GP, OP and a trained OT. The clinical occupational physician independently assesses the mental and physical condition of the patient and is responsible for the planning and the coordination of the continuation of care. First consultation of the clinical occupational physician will take place in the tenth or eleventh week after surgery. Table 2 presents an overview of the integrated care protocol. Depending on the diagnosis, the clinical occupational physician will work out a treatment and rehabilitation plan (with a RTW prognosis) and discuss it with the patient and her OP. If both agree with the plan, the recommendations will be executed by calling in the assistance of the OT (if relevant), the patients' employer and/or appropriate care provider(s). The patients' OP will not lose any responsibilities regarding the final RTW plan. Communication between medical care providers will be performed according to the GP-OP-coordination guideline [29]. Six and 12 weeks after the first consultation, the patient will visit the clinical occupational physician to evaluate the progress, discuss existing problems and if necessary adjust the date of RTW.

**Table 2 T2:** Integrated care and workplace intervention protocol

Weeks after surgery	Integrated care protocol ***Carried out by the clinical occupational physician***		Workplace intervention protocol ***Carried out by the Occupational Therapist (OT)***
**10-11**	First consultation: a. History taking and physical examination to identify: • adequacy of illness behaviour • presence of psychosocial problems • inadequate treatment • limitations at work influencing RTW (e.g. physical heavy work, organizational obstacles). b. Contact patients' other care providers (if relevant). c. Diagnosis of the medical situation or problem(s) d. Propose a treatment and rehabilitation plan (with a RTW prognosis). e. Discuss the treatment and rehabilitation plan with the patient and her occupational physician. If both agree	⤏	Contact OT to start the workplace intervention protocol (if relevant)

	↓		First consultation:
**12-13**	Call in the assistance of patients' employer and relevant care provider(s) Discuss the advisory plan (developed by the OT) with the OT	↔	a. Observation, inventory and ranking of patient's tasks and obstacles for RTW at the patients' workplace. b. Inventory and ranking patients' tasks and obstacles for RTW by the patients' employer. c. Patient, patients' employer and the OT brainstorm and discuss as many potential solutions as possible, for the problems identified in step a en b. d. Solutions are sorted and prioritized based on implementation time, costs and contribution to the problem(s). The OT reports (in consultation with the clinical occupational physician) an advisory plan specifying what has to be done, how, when and by whom. This report is sent to the patient, the patient's employer, OP and the clinical occupational physician.

**14-15**			Optional worksite visit to give additional instructions or training to the patient on working in the modified setting.

**16-17**	Second consultation: a. Evaluate the diagnosis, effect of the treatment and progress b. If necessary, adjust the date of RTW	↔	Evaluation between the patient, patients' employer and the OT (by telephone) with regard to the effects of the workplace adaptations. Further improvements are sought for when solutions have prove not to be totally effective.

**19-20**		←	Final report is sent to the patient, the patient's employer, OP and the clinical occupational physician.

**22-23**	Third and final consultation: a. Evaluate the diagnosis, effect of the treatment and progress b. If necessary, adjust the date of RTW c. Hand the employee over to her own OP		

Abbreviations: RTW = Return to Work, OT = Occupational Therapist; OP = Occupational Physician

##### Workplace intervention protocol

The workplace intervention procedure starts when the clinical occupational physician refers the patient to the OT, an expert to provide work (place) adaptations. The clinical occupational physician will define the conditions (working hours, duties, etc) under which the patient may return to work, which should be adopted by the OT and communicated effectively to the patient and the employer. The workplace intervention is based on methods used in 'participatory ergonomics' [30,31] and presumes strong commitment of both the patient and employer. This intervention has been developed originally for patients with chronic low back pain [30,32] and has shown to be (cost) effective in this population [33,34]. For this study, the protocol is adapted to post-operative gynaecological patients, regarding time-schedule and involved care providers. The consecutive steps of the workplace intervention protocol are described in table 2. The main aim of this intervention is patients' full RTW in their own or equal work. To achieve this aim, the OT will try to reach consensus between patient and her employer regarding feasible solutions for the obstacles for RTW. The solutions will be judged on short-term implementation possibilities, affordability and problem solving capability. After consensus has been reached, patient, patient's employer and OT will agree on an implementation plan, which will be evaluated during following weeks.

### Outcome Measures

#### Data-collection

The follow-up period will be 26 weeks after surgery (baseline). All the outcome variables are measured using self-report online questionnaires [35] and will be taken at baseline, 2, 6, 12 and 26 weeks after surgery. In general, the longer the recall period, the less accurate individuals are in reporting for example the use of health care services. Although no evidence on the optimal period is provided by literature, 12 and 26 weeks are frequently used and generally accepted [36]. Little agreement exists on the accuracy and validity of self-reported health care utilization and absenteeism data [37]. However, regarding sickness absence general consistency in the self-reporting can be relied on when recall is required within one month [37,38]. Therefore, in this study a monthly self-reported calendar of sickness absence per post was chosen to measure RTW. Furthermore, gynaecologists will complete questionnaires one day after surgery of each patient and at the end of the study. Employers will be asked to evaluate the e-health intervention eight weeks after the surgery of their employee. When patients, gynaecologists and employers do not fill out the questionnaires within one week, they will receive a reminder per email. If no response follows, they will be reminded by a telephone conversation. In addition to the questionnaires and calendars, the e-health intervention used by the intervention group will measure the use of the intervention, complications and (satisfaction with) recovery. Table 3 presents an overview of the outcomes and variables measured in this study.

**Table 3 T3:** Overview of outcome measures & variables in this study

Outcome measures & variables	T_0_ Baseline^d^	T_1_ 2 wks after surgery	T_2_ 6 wks after surgery	T_3_ 12 wks after surgery	T_4_ 26 wks after surgery
Primary					

1) Return to work^a^		measured monthly^e^			

Secondary					

2) Total duration of sick leave^a^		measured monthly^e^			

3) First RTW^a^		measured monthly^e^			

4) Recovery					

• Recovery specific QoL (RI-10)	X	X	X	X	X

• Performed activities			X		

• Performed activities measured by e-health intervention^b, c^		at least 2, 4, 7, 14, 21, 28, 42, 56, 84 days after surgery			

5) Functional and general health status (SF36, EuroQoL)	X			X	X

6) Pain intensity (Von Korff)			X	X	X

7) Empowerment (GSES)		X	X	X	

8) Health care usage (TicP)				X	X

9) Occurrence of complications during the post-operative period			X	X	X

• Complications measured by e-health intervention^b, c^		at least 7, 14, 21, 28, 42, 56, 84, 126 and 182 days after surgery			

Prognostic variables					

10) Socio-demographic variables	X				

11) Type of surgery	X				

12) Complications during surgery			X		

13) Work-related factors (DMQ, JCQ, additional questions)	X				

14) Pain perception and fear avoidance belief (Tampa scale)	X				

15) Sick leave duration in the past three months	X				

16) Expectations, intention and motivation for return to work	X				

Process evaluation					

17) Patients attitudes, opinions and compliance regarding the convalescence recommendations and tools of the e-health intervention^a^		X	X	X	X

18) Physicians' and employers' attitude en opinion regarding the multidisciplinary care program^b^				X	

19) Satisfaction with care program and care providers (e.g. PSOHQ)				X	

20) Use of the e-health intervention^b^		X		X	

21) Suggestions for improvement of the e-health intervention		X		X	

22) Provided convalescence recommendations by the care providers according to the patients		X			

^a ^Return to work and total duration of sick leave is measured by a monthly calendar of sickness absence.

^b ^Only measured in the intervention group

^c ^Besides the standard requested time points, the patients can fill out the recovery monitor/complication form as many times as requested

^d ^The baseline questionnaire will be filled out no longer than four weeks before the day of surgery.

^e ^Measured from day of surgery

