**Methods/Design:**

We designed a randomized controlled trial to assess the effect of the multidisciplinary care program on full sustainable return to work in patients after gynaecological surgery, compared to usual clinical care. Two hundred twelve women (18-65 years old) undergoing hysterectomy and/or laparoscopic adnexal surgery on benign indication in one of the 7 participating (university) hospitals in the Netherlands are expected to take part in this study at baseline. The primary outcome measure is sick leave duration until full sustainable return to work and is measured by a monthly calendar of sickness absence during 26 weeks after surgery. Secondary outcome measures are the effect of the care program on general recovery, quality of life, pain intensity and complications, and are assessed using questionnaires at baseline, 2, 6, 12 and 26 weeks after surgery.

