#### Secondary Outcome measures

2) The total duration of sick leave (due to the consequences of the surgery) during the 26 weeks follow-up period; measured by a monthly calendar of sickness absence.

3) First RTW; measured by a monthly calendar of sickness absence.

4) Recovery; measured by a validated Recovery Specific Quality Of Life questionnaire RS-QOL(RI10) [40], an extended list of (graded) activities based on the detailed convalescence recommendations given to the patients of the intervention group [18] and a recovery monitor which is a tool of the e-health intervention of the intervention group.

5) Functional and general health status (Quality of life); assessed according to the standard Dutch version of the EuroQol [41] and the Short-form health survey (SF-36) [42,43].

6) Pain intensity; measured using Von Korff questionnaire [44].

7) Empowerment; assessed by the Dutch adaptation of the General Self-Efficacy Scale [45].

8) Health care usage; measured by the Tic-P questionnaire [46] and valued according to the prices in the guidelines for economic evaluation in the Netherlands [47].

9) The occurrence of complications in the post-operative period; assessed by questions based on the complication registration form of The Dutch Society of Obstetrics and Gynaecology (NVOG) [48]. Patients in the intervention group do also answer these questions more frequently through a tool of the e-health intervention, in order to register possible side effects of the intervention and to determine and inform them when symptoms require additional consultation of care providers or adaptation of convalescence recommendations.

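### The stated five-point schedule for the outcomes conflicts with Table 3, which gives pain intensity (Von Korff) and empowerment (GSES) no baseline reading, so neither can be adjusted for its own starting value

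*Protocol article*

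**What the plan says.** The Data-collection section opens with a general statement: "All the outcome variables are measured using self-report online questionnaires", and these "will be taken at baseline, 2, 6, 12 and 26 weeks after surgery". The abstract (Methods/Design) says that the secondary outcomes, which it lists as general recovery, quality of life, pain intensity and complications, "are assessed using questionnaires at baseline, 2, 6, 12 and 26 weeks after surgery".

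Table 3, in the same Data-collection section, sets out the times outcome by outcome:

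- "6) Pain intensity (Von Korff)" is marked at 6, 12 and 26 weeks.
- "7) Empowerment (GSES)" is marked at 2, 6 and 12 weeks.
- "5) Functional and general health status (SF36, EuroQoL)" is marked at baseline, 12 and 26 weeks.
- "Recovery specific QoL (RI-10)" is marked at all five times.

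Pain intensity is named in the secondary objectives. Empowerment is listed among the secondary outcome measures. The Data analysis section provides for adjustment only where the arms turn out to differ on prognostic characteristics at baseline.

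**The concern.** Two schedules stand in the current text and cannot both be right. A reader of the abstract would expect a baseline pain score, and a reader of the Data-collection text would also expect a baseline GSES. Table 3 provides neither.

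If Table 3 is what will be done, two secondary outcomes have no reading before randomisation. This has three consequences:

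- The arms can be compared only on follow-up values, without the gain in precision that a scale's own baseline usually brings.
- The baseline comparison in the Data analysis section cannot show a chance imbalance on either scale, so the conditional adjustment planned there cannot act on one.
- Change in empowerment cannot be described. This matters because empowering patients is the declared aim of the website (Multidisciplinary care program; Step 1). Access opens about four weeks before surgery, and the first GSES reading comes two weeks after it.

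**Working it through.** **1. The stated schedule against Table 3**

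| Outcome (patient questionnaire) | Baseline | 2 wk | 6 wk | 12 wk | 26 wk |
|---|---|---|---|---|---|
| Text, all outcomes | X | X | X | X | X |
| RI-10 | X | X | X | X | X |
| Performed activities | – | – | X | – | – |
| SF-36, EuroQol | X | – | – | X | X |
| Von Korff pain | – | – | X | X | X |
| GSES | – | X | X | X | – |
| Health care usage | – | – | – | X | X |
| Post-operative complications | – | – | X | X | X |

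Each of these Table 3 rows has five cells under the five time headings, so the blanks are not shifted cells. Only the RI-10 follows the stated schedule. A missing baseline is natural for post-operative complications. It is not natural for pain or self-efficacy, which both exist before surgery.

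**2. Exposure before the first GSES reading**

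Access from four weeks before surgery plus two weeks after surgery gives 4 + 2 = 6 weeks. This is an upper bound, because women are randomised once surgery is scheduled within four weeks.

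**3. The plan's own figure**

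The Sample size section gives 191 patients for a hazard ratio of 1.5, 5% significance and 80% power. Schoenfeld's formula with equal allocation and a two-sided test reproduces it:

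4 × (1.960 + 0.842)² / (ln 1.5)² = 191.

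Allowing for 10% dropout, 191 / 0.9 = 212.2, against 212 stated. The point does not depend on this calculation. It only supplies the 191 used below.

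**4. What a baseline would add**

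Inputs: 191 women with data, split equally (95.5 per arm); two-sided 5%; 80% power. The documents give no baseline-to-follow-up correlation r, so r = 0.3 to 0.7 is assumed.

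- Unadjusted detectable standardised difference: (1.960 + 0.842) × √(2 / 95.5) = 0.405.
- Adjustment for baseline multiplies the variance by 1 − r² and the detectable difference by √(1 − r²).

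| r (assumed) | Variance factor | Variance reduction | Detectable difference |
|---|---|---|---|
| none | 1.00 | 0% | 0.405 |
| 0.3 | 0.91 | 9% | 0.387 |
| 0.5 | 0.75 | 25% | 0.351 |
| 0.7 | 0.51 | 49% | 0.290 |

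Equivalently, the unadjusted comparison needs 1 / (1 − r²) = 1.10, 1.33 or 1.96 times as many women for the same precision.

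**The case against.** The strongest reply is that the contradiction is editorial. The Data-collection text refers the reader to Table 3, and the questionnaire columns of that table are together exactly baseline, 2, 6, 12 and 26 weeks. The sentence may mean only that questionnaires go out at those times. That is a plausible reading, but it is not what the sentence says. The abstract attaches the same times to pain by name. Rewording would also not supply the missing baselines.

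A second reply is that the missing baselines matter little. Randomised arms can be compared on follow-up values without bias. The trial is powered on return to work, which comes from a monthly calendar and is unaffected. Other baseline measures (RI-10, SF-36, EuroQol and the Tampa scale for pain perception and fear avoidance) could serve as covariates. Empowerment is not named in the secondary objectives. All of this stands and limits the weight of the point. None of these measures is the Von Korff score or the GSES itself, however, so the own-scale adjustment and any description of change in empowerment remain unavailable.

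A reader might infer more from Table 3 than it supports:

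- **That quality of life goes unread until week 12.** The Secondary Outcome measures section does attach that label to the generic instruments ("5) Functional and general health status (Quality of life); assessed according to the standard Dutch version of the EuroQol" and the SF-36). But the RI-10, a recovery-specific quality-of-life scale, is read at 2 and 6 weeks. Early recovery is therefore observed, and adding EuroQol at those times would be a choice of instrument.
- **That all three outcomes share one defect.** SF-36 and EuroQol have a baseline and can be adjusted for it. Pain is read at 6 weeks and empowerment at 2 and 6 weeks, so both are observed during recovery.
- **That large pre-operative differences go uncorrected.** The documents give no evidence on the size of such differences.

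**Conclusion.** The point holds in a limited form. The Data-collection text and the abstract contradict Table 3. If Table 3 governs, Von Korff pain and the GSES have no reading before randomisation. The consequence is lost precision on two secondary outcomes and no measure of change in empowerment. It is not bias, and it does not reach the primary outcome.

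The size depends on a correlation that the documents do not give. At r = 0.3 the loss is small (detectable difference 0.41 against 0.39). At r = 0.7 it is material (0.41 against 0.29). These figures also assume that 191 women in equal arms supply the data. The change is worth making because a pre-randomisation questionnaire already exists and one of the two scales measures the construct that the website targets.

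**What to change.** - Add the Von Korff questionnaire and the GSES to the baseline questionnaire that is already completed before randomisation, and mark both at baseline in Table 3.
- Compare the arms on these two outcomes with adjustment for the baseline value, as a planned analysis that does not wait for an observed imbalance.
- Reword the abstract and the Data-collection text to say that questionnaires are sent at baseline, 2, 6, 12 and 26 weeks and that each outcome is measured at the times in Table 3. If the text is what was intended, correct Table 3 instead.

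Cost: a slightly longer online baseline questionnaire and no extra contact. Women already enrolled would lack the two readings, so the analysis would have to state how they are handled.

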### Multidisciplinary care program

Based on the results of the modified Delphi study, the outcomes of the focus group discussions, the literature review and considering both the ICF model as well as the Attitude, Social influence and self-Efficacy (ASE) model in which important determinants of recovery and RTW are described [20,21], a multidisciplinary care program for gynaecological patients undergoing surgery was developed. The care program aims at the different aspects of curative treatment as well as at personal and external factors. In addition, it tries to encourage patients in resuming activities and participation in the society. The program consists of an interactive e-health intervention, integrated care management and a participatory workplace intervention. The e-health intervention was developed through an intervention mapping protocol [22] and specifically aims at the empowerment of gynaecological patients and their environment during the pre- and postoperative period (from around four weeks before until eight weeks after surgery) [17]. This includes encouragement of patients in resuming daily and work activities. If the patient is still on sick leave 10 weeks after surgery, the integrated care management and participatory workplace intervention will be offered. This part of the intervention is based on a previous study with patients with chronic low back pain [23], and was adapted to our target group for this study.

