### Objectives

The main objective of this study is to evaluate the effectiveness of the multidisciplinary care program (e-health intervention, integrated care management & participatory workplace intervention) compared to usual care regarding full sustainable RTW for patients after hysterectomy or laparoscopic adnexal surgery on benign indication. Secondary objectives of the study are 1) to study the effect of the multidisciplinary care program on general recovery, quality of life, pain intensity and complications; 2) to investigate how the program is evaluated by the patients, their health care providers and their employers and 3) to validate the multidisciplinary convalescence recommendations developed in het Delphi study [18].

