#### Step 2: if sick leave exceeds ten weeks, additional integrated care management including workplace intervention will be offered

This part of the intervention will only be offered to the patient when she is not fully returned to work ten weeks after surgery and consists of two main protocols; 1) Integrated care protocol and 2) Workplace intervention protocol and is based on a previous study of patients with chronic low back pain [23].

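### Patient satisfaction and employer opinion are each read once, at week 12 or earlier, so neither is measured after step 2 (integrated care and workplace intervention) has been delivered

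*Protocol article*

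**What the plan says.** **The objective.** Under Objectives, the second of the secondary aims is "to investigate how the program is evaluated by the patients, their health care providers and their employers". The section Multidisciplinary care program defines what is to be rated: "The program consists of an interactive e-health intervention, integrated care management and a participatory workplace intervention".

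**When step 2 happens.** The Step 2 section states: "This part of the intervention will only be offered to the patient when she is not fully returned to work ten weeks after surgery". Under Integrated care protocol, "First consultation of the clinical occupational physician will take place in the tenth or eleventh week after surgery", and then "Six and 12 weeks after the first consultation, the patient will visit the clinical occupational physician to evaluate the progress". Table 2 puts the occupational therapist's first contact with patient and employer in weeks 12-13, an optional worksite visit in weeks 14-15 and a telephone evaluation in weeks 16-17. The closing step for the therapist is in weeks 19-20: "Final report is sent to the patient, the patient's employer, OP and the clinical occupational physician".

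**When opinions are collected.** Table 3 gives item 19, "19) Satisfaction with care program and care providers (e.g. PSOHQ", a single mark, in the T3 (12-week) column. Item 18, the attitude and opinion of physicians and employers on the multidisciplinary programme, also has a single mark at T3. Neither is marked at T4 (26 weeks). The Data-collection text gives a different time and a narrower subject for employers: "Employers will be asked to evaluate the e-health intervention eight weeks after the surgery of their employee". It has gynaecologists responding the day after each operation and again when the study ends.

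**The concern.** The objective covers the full programme, but the two items that ask about the programme as a whole are read when step 2 has barely started. A woman who enters step 2 gives her only satisfaction rating around the time the therapist first comes to her workplace. Her employer is asked at that same point or, by the text, two weeks before step 2 can begin.

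This matters because step 2 is the part whose acceptability is least certain. The Workplace intervention protocol section says it relies on strong commitment from both patient and employer. It was developed for chronic low back pain and adapted to this population, and Strengths and limitations notes that one physician and one therapist deliver it. If the 8- and 12-week answers are reported as views of the care programme, readers will take them to cover a component that the respondents had hardly met.

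**Working it through.** No estimate is involved. The check sets the delivery schedule against the measurement schedule, both as printed in the protocol article.

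**1. Consistency of the delivery schedule.** The first physician consultation is in week 10 or 11. Adding the stated intervals gives:
- second: 10 + 6 = 16 to 11 + 6 = 17, i.e. weeks 16-17
- third: 10 + 12 = 22 to 11 + 12 = 23, i.e. weeks 22-23

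Both agree with Table 2, so the text and the table give one timetable for step 2.

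**2. Scheduled step 2 contacts.**
- Clinical occupational physician, three consultations: weeks 10-11, 16-17 and 22-23.
- Occupational therapist, four steps: first contact 12-13, optional visit 14-15, telephone evaluation 16-17, final report 19-20.

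**3. Contacts completed at each reading.** A contact counts as completed when its scheduled window has closed before the week in question.

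| Week | Reading | Physician consultations completed | Therapist steps completed |
|---|---|---|---|
| 8 | Employers, by the text | 0 of 3 | 0 of 4 |
| 12 | Items 18 and 19, by Table 3 | 1 of 3 | 0 of 4 (the first may be starting) |
| 13 | Item 19 answered a week late (12 + 1) | 1 of 3 | 0 of 4 |
| 26 | T4, where neither item is scheduled | 3 of 3 | 4 of 4 |

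The week 13 row is included because reminders go out after one week without a reply. A late answer does not change the counts.

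**4. Whether another listed measure fills the gap.**
- Item 17 is asked of patients up to week 26, but covers only the convalescence recommendations and the e-health tools.
- Items 20 and 21 concern the e-health intervention and have no mark after T3.
- Item 22 is asked at week 2 only.
- The telephone evaluation in weeks 16-17 involves patient and employer, but it belongs to the intervention, includes the therapist who delivers it, and is not a listed outcome.

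So no listed reading of patient satisfaction or employer opinion falls after step 2.

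**5. Agreement between the two measurement schedules.** For employers the text says week 8 and the e-health part, while Table 3 says week 12 and the whole programme. For physicians the text has gynaecologists at day 1 and at the end of the study, while Table 3 marks week 12. The two cannot both be the full schedule for item 18.

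**The case against.** The strongest reply is that the article may not show the whole process-evaluation schedule. The columns of Table 3 are the patients' time points, and they leave out the gynaecologists' forms and the week-8 employer form. The section on outcomes regarding process evaluation says all three groups get questions on the multidisciplinary programme and gives no times. This has some force for employers and physicians. It has little for item 19, a patient item that Table 3 places at T3 and not at T4. For employers, both times that the article does give precede the workplace intervention or coincide with its start. These are stated timings, not omitted ones.

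Three stronger readings are tempting, and the document supports none of them.
- **A reader might infer that objective 2 cannot be answered at all for step 2.** It has three groups of raters. Gynaecologists, whom the Discussion names as part of the step 2 team, respond at the end of the study, and the first physician consultation can be rated at week 12.
- **A reader might infer that the 12-week data reflect the website alone.** By then a step 2 patient has had a full first consultation, and every intervention patient should have received standardised recommendations from her care providers. The therapist's first contact, which involves the employer, may also have begun in week 12.
- **A reader might infer that a result for step 2 could not be interpreted.** No separate step 2 effect is planned. The randomised comparison is of the whole programme with usual care, with sick leave recorded monthly to week 26.

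Two limits on the weight of the point also stand. Step 2 reaches only women not fully back at work at ten weeks, and its workplace part only where relevant. The process evaluation is confined to the intervention group.

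**Conclusion.** The point holds in a limited form. Patients' satisfaction with step 2 and employers' opinion of it are not measured after step 2 is delivered, so that part of secondary objective 2 is left largely unanswered. At the later of the two stated times, week 12, a step 2 patient has had one of three physician consultations and none of the four therapist steps is complete. At week 8 the count is zero for both.

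This assumes that contacts follow the weeks in Table 2 and that Table 3 and the Data-collection text together give the schedule for patients and employers. The article does not say how many women are expected to enter step 2. They are some fraction of the roughly 106 allocated to the programme (212 / 2), so the number of respondents affected is unknown.

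The primary outcome, the sample size, the main effectiveness analysis and the gynaecologists' end-of-study questionnaire are untouched. This is a badly placed secondary measurement that is worth correcting because correction is cheap. It does not threaten the trial's main conclusion.

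**What to change.** - For women who entered step 2, repeat item 19 in the existing 26-week (T4) questionnaire. T4 falls at least three weeks after the last scheduled consultation (26 - 23 = 3).
- Send the employers of these women the item 18 questions, covering the workplace intervention, after the therapist's final report or at week 26.
- Keep the early readings, but report the 8- and 12-week data as evaluating mainly step 1.
- Reconcile the Data-collection text (employers at week 8 on the e-health part; gynaecologists at day 1 and end of study) with item 18 in Table 3 (week 12, whole programme), and state one schedule for each group of raters.

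The cost is a few extra questions in a questionnaire already being sent and one additional form for a subset of employers. The downside is slight respondent burden and some employer non-response, so the number of employers approached and the number replying should be reported with the results.
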